### Study timeline

#### Recruitment

During recruitment (also called the pre-baseline visit), the client will be given a MEMS cap, which will be used to track baseline adherence and study eligibility for 2–3 months (depending on the date of the client’s next scheduled clinic visit). During the recruitment phase, clients will be consented to participate by study coordinators, and for some (about 120 in total), we will administer short, 30-min qualitative interviews (Section 2.13.2). Participants will be compensated with 20,000 USh for their time. They will be paid for completing questionnaires even if this does not happen on a scheduled clinic visit, such as when they come in late or early for a clinic appointment.

As appointment dates are readily available from the electronic medical records system, we can print out weekly lists of eligible clients together with when they are expected at the clinic and when they are scheduled for their next viral load test. We will enroll clients on the day of or within 3 months of their annual viral load test to synchronize the viral load testing with the study timeline. Doing so will allow us to benefit from existing clinic procedures and reduce the inconvenience and transport costs of the intervention for clients. Thus, participants will not take any additional viral load tests or attend additional clinic visits for the study. We will provide this list of participants to the study coordinator, who can then watch out for these clients in collaboration with the clinic receptionist.

We will consent and enroll 4–6 clients per day (some clients may refuse participation, though this has been rare in our previous studies) during the 6- to 9-month recruitment period. Based on the large clinic population and our previous experience, we expect to recruit 330 clients easily within a 6-month period but we have allowed sufficient extra time to accommodate for the clinic being closed on public holidays and for any other delays.

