#### Baseline survey and randomization

When a client returns for their next scheduled clinic visit after recruitment (after about 2–3 months), we will conduct the baseline survey, reveal their treatment assignment to either the control or one of the two intervention groups, and begin the intervention. We will exclude all clients who did not open the MEMS cap for at least 30% of the days during the pre-baseline period as consistent use of the MEMS cap is essential for participation in the study. This second visit will (just as the first one) coincide with a scheduled clinic visit so that participants do not have to come to the clinic solely to participate in study activities.

The baseline survey contains information about:
demographics and socioeconomic status, including age, gender, education, relationship status, employment type and status, income, housing, economic shocks, and household compositionmedical history, including history of opportunistic infections, health-seeking behavior, current medications and length of time on current drug regimen, and WHO HIV disease stage, some of which will be taken from their medical recordsphysical symptoms and side effects, for example, respondents will be asked how “bothersome” and “disruptive” (in separate items) any symptoms perceived to have been caused by their medication in the past month have beenreasons for non-adherence or failure to seek care; we will use an 11-item module regarding reasons for non-adherence developed by the AIDS Clinical Trials Group that we slightly modified to fit the Ugandan context that asks participants to indicate whether listed items were reasons for not taking their medication in the previous month or seeking care, such as “when the drugs make you feel bad,” or “when your daily routine is interrupted,” or “lacked resources”

We use the Intrinsic Motivation Inventory to examine participants’ subjective experiences of taking medications [47]. The survey will also collect information on behavioral economics biases, such as present bias or risk preferences.

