### Sample size and power

We have calculated the size of effects that our sample will be able to detect with 80% power (two-tailed test) with regard to outcomes at months 12 and 24, and 10% attrition every year (we observed 5% attrition over 20 months in our previous studies so this is a conservative estimate). For the primary outcome of viral suppression, we use a conservative estimate of 70% of clients in the control group showing suppression, based on discussions with the Mildmay team. Our sample size of 110 participants in each of the three arms (total *n* = 330) will be able to detect a 7 percentage point difference for joint comparison of T1 and T2 against the control group at month 12, and about an 8.5 percentage point difference between the two intervention arms (a subgroup analysis). The corresponding differences at month 24 are 8 and 9 percentage points, respectively. These are considered small effect sizes (Cohen’s *d* of between .15 and .185), which we will be able to detect. For adherence, in our previous study we observed mean adherence rates of ~75% as measured by MEMS caps. Our sample size of 110 in each of the intervention arms and the control group will provide sufficient power to detect about a 6.5 percentage point difference in mean adherence between the two intervention arms (combined) and the control group. To test for differences in adherence between the two intervention arms, our study is powered to detect about a 7.5 percentage point effect as measured by MEMS caps. Again, this means we will be able to detect small effects. The corresponding differences we will be able to detect at month 24 are about 7 and 8 percentage points, respectively. Our main econometric models will include covariates that will improve precision. Therefore, these minimum detectable effects reported above are likely upper bounds.

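### The detectable differences start from a full 110 per arm, but 330 is counted before the MEMS run-in and the run-in loss is not allowed for

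*Protocol article*

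**What the plan says.** **What 330 counts.** Sampling and participants says that 330 clients will be recruited. Recruitment identifies recruitment with the pre-baseline visit, at which clients consent and receive the cap, and adds that "we expect to recruit 330 clients easily within a 6-month period". The abstract divides the 330 into 110 per arm.

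**What happens next.** Baseline survey and randomization, describing the following scheduled visit after about 2–3 months, says: "We will exclude all clients who did not open the MEMS cap for at least 30% of the days during the pre-baseline period". Exclusion criteria gives the same rule and adds that these clients hand back the cap and make no more study visits. The intervention begins only after this step.

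**What the power statement uses.** Sample size and power works from "Our sample size of 110 participants in each of the three arms" at 80% power, two-tailed. Its one allowance for loss is "10% attrition every year", supported by the remark that "we observed 5% attrition over 20 months in our previous studies so this is a conservative estimate". For adherence it gives detectable differences of about 6.5 points (pooled arms against control) and 7.5 points (T1 against T2), and about 7 and 8 points at month 24. For viral suppression it gives 7 and 8.5 points at month 12, and 8 and 9 at month 24. The run-in is not mentioned there.

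**The concern.** The number recruited and the number starting the intervention are different quantities, separated by an exclusion rule and by a 2–3 month gap in which clients may also fail to return. The power statement gives the first number the role of the second. If the run-in removes anyone beyond what the attrition allowance covers, the evaluable sample is smaller than assumed, the true detectable differences are larger than stated, and power at the stated differences is below 80%. A reader who judges a null result, or the T1 versus T2 comparison, against those figures would credit the trial with more sensitivity than it has.

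This point concerns only the size of the analysed sample. Whether the exclusion falls before or after allocation, and any bias that follows, is a separate question.

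**Working it through.** **Inputs from the article:** 110 per arm; 10% attrition per year; 80% power, two-tailed; adherence differences 6.5/7.5 (month 12) and 7/8 (month 24); control suppression 70%; earlier attrition 5% over 20 months.

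**Assumptions:** alpha 0.05 (the level is not stated); run-in loss x of 5%, 10% and 20% (not given).

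**Step 1. Numbers behind the stated differences.** With attrition only, n is 110 × 0.9 = 99 per arm at month 12 and 110 × 0.9² = 89.1 at month 24.

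**Step 2. Can the stated figures be reproduced?** The adherence figures cannot be checked independently because no SD is given, so they are taken as exact at 80% power. The viral suppression figures can be checked. For the pooled comparison at month 12 (99 controls, 198 in the pooled arms, control 0.70), a difference of 14.2 points (0.70 against 0.842) satisfies the two-proportion formula:

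- pooled proportion (0.70 + 2 × 0.842)/3 = 0.795; null term 1.96 × sqrt(0.795 × 0.205 × (1/99 + 1/198)) = 0.097
- alternative term 0.842 × sqrt(0.70 × 0.30/99 + 0.842 × 0.158/198) = 0.044
- sum 0.142, or 14.2 points, against the stated 7

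The other three come to 16.4 (stated 8.5), 14.9 (stated 8) and 17.1 (stated 9). These do not reproduce even with x = 0, so the run-in is not the cause.

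**Step 3. Effect of a run-in loss on adherence.** Evaluable n is 110 × (1 − x) × 0.9 per year. A detectable difference scales as 1/sqrt(n), so it grows by 1/sqrt(1 − x). Power at the stated difference is Φ(2.80 × sqrt(1 − x) − 1.96), where 2.80 = 1.96 + 0.84. For x = 10%: 2.80 × 0.949 − 1.96 = 0.70, and Φ(0.70) ≈ 0.76.

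| Run-in loss (assumed) | Starting per arm | n, month 12 | n, month 24 | Factor | Adherence, month 12 | Adherence, month 24 | Power at stated difference |
|---|---|---|---|---|---|---|---|
| 0% | 110 | 99 | 89 | 1.000 | 6.5 / 7.5 | 7 / 8 | 80% |
| 5% | 104.5 | 94 | 85 | 1.026 | 6.7 / 7.7 | 7.2 / 8.2 | 78% |
| 10% | 99 | 89 | 80 | 1.054 | 6.9 / 7.9 | 7.4 / 8.4 | 76% |
| 20% | 88 | 79 | 71 | 1.118 | 7.3 / 8.4 | 7.8 / 8.9 | 71% |

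**Step 4. How much the attrition allowance could absorb.** If attrition ran at the earlier rate, retention would be 0.95^(12/20) = 0.970 at month 12 and 0.95^(24/20) = 0.940 at month 24. The allowance assumes 0.90 and 0.81. The run-in loss that just uses up the difference is 1 − 0.90/0.970 ≈ 7% at month 12 and 1 − 0.81/0.940 ≈ 14% at month 24.

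**The case against.** The strongest defence is the slack in Step 4: at the earlier attrition rate, a run-in loss of up to about 7% (month 12) or 14% (month 24) would leave the evaluable numbers intact. Handling missing data and attrition also reports past attrition well below 10% a year, and the power section expects covariates to improve precision. Exclusion criteria calls true adherence under 30% very rare. Yearly attrition may also be meant to run from recruitment, in which case non-return at the second visit already falls inside it.

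Much of this stands as a limit on size. It does not remove the gap. The slack is presented as caution about yearly attrition, not as a run-in allowance, and the article does not say whether the earlier 5% included a run-in. The rarity remark concerns true adherence, whereas the rule is said to target people unable or unwilling to use the cap, whose frequency is not given. The covariate gain is not quantified.

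Inclusion criteria calls 330 the study sample, which could be read as a count after exclusions. The recruitment text points the other way, so the meaning at least needs settling.

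Three stronger readings are tempting and are not supported:

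- A reader might infer from the adherence figures that no run-in loss was built in, because they imply nearly one SD with 99 and 89 per arm (18.8 to 19.3 points). But a run-in loss multiplies every n by the same factor. At 10% loss the implied SDs are 17.9 to 18.3, just as coherent. The evidence is the wording of the power section, not the SD.
- A reader might conclude that the promised power is certainly missed. The loss is unknown and may be absorbed.
- A reader might blame the run-in for the viral suppression figures. A 10% loss would move the stated 7 points only to 7.4. The gap to about 14 has another source.

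**Conclusion.** The point holds in a limited form. The article counts 330 before the run-in, removes clients afterwards, and carries the full 110 per arm into the power calculation with yearly attrition as the only allowance. The stated differences are therefore understated by 1/sqrt(1 − loss), to the extent that conservatism in the attrition figure does not cover the loss.

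The effect on adherence is modest: at an assumed 10% loss, about 0.4 points on each difference and about 4 percentage points of power. This rests on a two-sided 5% level, on run-in losses that are assumptions, and on taking the stated adherence differences as exact. It is a correction to how the trial's sensitivity is reported and does not undermine the design.

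**What to change.** 1. In Sampling and participants and in Inclusion criteria, say that 330 is the number recruited before the run-in.
2. In Sample size and power, report the run-in loss observed so far (Trial status says that recruitment is underway), and compute evaluable n as 110 × (1 − run-in loss) × 0.9 per year. Give the resulting detectable differences with the alpha level and the adherence SD used.
3. Say whether the 10% yearly attrition is meant to include run-in losses and from which visit it is counted. If it is meant to include them, drop the claim that it is conservative or justify that claim against the combined loss.
4. Recalculate the viral suppression differences separately. Adding a run-in allowance to the present 7, 8.5, 8 and 9 points would not repair them.

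Items 1 to 3 cost a few sentences and adherence figures that are slightly less favourable. They need no extra patients and no change of design. Item 4 will change the viral suppression figures substantially, for reasons unrelated to the run-in.

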### Limitations

This study has several limitations. First, the study will include only 330 patients from one clinic in Uganda. Although our sample size is well powered to detect clinically important effects, it is not clear that our results will extrapolate to other areas of Uganda or other countries. Second, while our study includes both large and small incentives, we are unable to disentangle the effect of these different incentive types and the extent to which there is a dose response with incentive size. The impact of offering different incentive types and amounts will require further research. We also cannot verify the longer-term effects of these incentives or whether any effects persist after the incentives are withdrawn beyond the 12-month period during which we will monitor the effects of the intervention. Third, although adherence is measured using MEMS caps, which is currently one of the most accurate ways to measure adherence, we cannot exclude the possibility that some participants will consciously manipulate the pill bottle openings to increase their chances of receiving the incentives. 

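### The stated detectable differences in viral suppression (7 to 9 points) are about half of what 110 per arm can detect with 80% power

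*Protocol article*

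**What the plan says.** The section Sample size and power reports the "size of effects that our sample will be able to detect with 80% power (two-tailed test"), allowing for 10% attrition every year. For viral suppression, the biological primary outcome, "we use a conservative estimate of 70% of clients in the control group showing suppression". It then states that 110 per arm "will be able to detect a 7 percentage point difference for joint comparison of T1 and T2 against the control group at month 12"; for T1 versus T2 it gives roughly 8.5 points. For the later time point, "The corresponding differences at month 24 are 8 and 9 percentage points, respectively". It describes these as small effects, with Cohen's d between .15 and .185.

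The paragraph closes by noting that covariates will add precision: "Therefore, these minimum detectable effects reported above are likely upper bounds". The Limitations section says that "our sample size is well powered to detect clinically important effects".

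Two inputs are not given. The significance level is missing (the text says only two-tailed), and so is a reference suppression rate for T1 versus T2, since the 70% is given for the control group alone.

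**The concern.** With a binary outcome near 70% and about 100 people per arm, the standard error of a difference between two arms is roughly 6 points. A difference detectable with 80% power must be about 2.8 standard errors, so figures of 7 to 9 points look too small by a factor of two.

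The stake is how the trial is read. A non-significant result on suppression could be taken as evidence against effects of 7 to 9 points, although the trial would miss such effects about two times in three or more. T1 versus T2 is the most exposed comparison. The Discussion asks whether rewarding suppression is as effective as rewarding measured adherence, and a non-significant difference would say little about that when only differences of 14 to 17 points are reliably detectable.

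**Working it through.** **Inputs.** From Sample size and power: 110 per arm; 10% attrition per year, hence 110 × 0.9 = 99 per arm at month 12 and 110 × 0.81 = 89.1 at month 24; control rate 0.70; power 80%; two-tailed. From Randomization: 1:1:1, so pooled versus control is 2:1 and T1 versus T2 is 1:1. Assumed: alpha 0.05.

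**The article's own d.** The SD of a binary outcome at 70% is √(0.7 × 0.3) = 0.458. Then 0.07/0.458 = 0.153 and 0.085/0.458 = 0.185. These match the stated .15 and .185, so the article's scale is the difference divided by 0.458.

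**The article's differences.** These do not reproduce. The detectable difference Δ = p₂ − p₁ solves

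Δ = 1.96 × SE₀ + 0.842 × SE₁,

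where SE₀ = √[p̄(1−p̄)(1/n₁+1/n₂)], p̄ is the average rate weighted by arm size, and SE₁ = √[p₁(1−p₁)/n₁ + p₂(1−p₂)/n₂].

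Worked case, pooled versus control at month 12 (n₁ = 99, n₂ = 198, p₁ = 0.70): at p₂ = 0.842, p̄ = 0.795, SE₀ = 0.0497 and SE₁ = 0.0529. Then 1.96 × 0.0497 + 0.842 × 0.0529 = 0.142, so Δ is 14.2 points.

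Power at the stated 7 points: p̄ = 0.747, SE₀ = 0.0535, SE₁ = 0.0549, and (0.07 − 1.96 × 0.0535)/0.0549 = −0.64, which gives power of 26%.

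| Comparison | Reference rate | Stated (points) | Derived (points) | Power at stated |
|---|---|---|---|---|
| Pooled vs control, month 12 | 70% | 7 | 14.2 | 26% |
| Pooled vs control, month 24 | 70% | 8 | 14.9 | 30% |
| T1 vs T2, month 12 | 70% | 8.5 | 16.4 | 28% |
| T1 vs T2, month 12 | 77% | 8.5 | 14.4 | 33% |
| T1 vs T2, month 24 | 70% | 9 | 17.1 | 28% |
| T1 vs T2, month 24 | 78% | 9 | 14.7 | 35% |

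The 77% and 78% rates are the control rate plus the stated pooled effect (70 + 7 and 70 + 8). Simulation of the pooled z test from a 70% reference (200,000 runs per case) gave power of 26%, 30%, 28% and 28% for the four stated differences, in the order of the table.

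**Attempts to rescue the stated figures.**
- No attrition (110 per arm): 13.6 points pooled and 15.6 points T1 versus T2 from 70%.
- Two-sided 0.10: power of 37% to 42% at the four stated differences from 70%. Two-sided 0.20: 51% to 56%.
- Covariates: from a 70% reference they would have to remove 1 − (stated/derived)² of the outcome variance, for example 1 − (7/14.2)² ≈ 0.76. Over the four figures this is 0.71 to 0.76. The text also presents covariates as a gain beyond the stated figures, so they are not already in them.
- Participants needed for 7 points at 80% power: 462 control plus 924 pooled, 1,386 evaluable, against 3 × 99 = 297 expected at month 12.

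**Corrected d on the article's scale.** 14.2/45.8 = 0.31, 16.4/45.8 = 0.36, 14.9/45.8 = 0.32 and 17.1/45.8 = 0.37. The direct formula 2.80 × √(1/n₁ + 1/n₂) gives 0.345, 0.398, 0.364 and 0.420, but that is a different standardisation and should be named if it is used.

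**A possible cause, unconfirmed.** Putting the variance 0.21 where the SD 0.458 belongs gives 2.80 × 0.21 × √(1/n₁ + 1/n₂) = 7.2 and 8.4 points at month 12 and 7.6 and 8.8 at month 24, close to the stated 7, 8.5, 8 and 9.

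**Sensitivity to the control rate** (pooled, month 12): 16.8 points at 50%, 15.9 at 60%, 14.2 at 70% and 11.7 at 80%.

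**The case against.** The strongest objection is that not every input is stated. Alpha is missing, and the 70% rate belongs to the control group only, so the T1 versus T2 figures rest on an assumed reference rate. This stands, and it is why T1 versus T2 is given as a range. It does not rescue the stated values: power is about a third at best from a 77–78% start, and looser levels leave it well below 80%.

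A second objection is that the upper-bound and well-powered statements also cover MEMS adherence. This stands too. The adherence differences of 6.5, 7.5, 7 and 8 points agree with one another at an SD of about 19 points, and no error is shown there. A reader might infer that the whole power paragraph is unsound, or that the adherence SD has been wrongly left out. The document does not support that, and a condensed article may leave the SD to the full protocol.

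A reader might also infer that 70% cannot be conservative because participants must have had recent adherence problems. The document does not settle this. Lack of suppression is one of three alternative entry routes, beside adherence counselling and WHO stage 3 or 4, and the 70% came from discussion with the clinic team. The point here does not depend on it.

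Finally, the data-analysis section plans estimated risk differences for every pair of arms, so interpretation need not rest on the power paragraph. That softens the consequence but leaves the printed figures wrong.

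**Conclusion.** The concern holds for viral suppression. On the article's inputs and a two-sided 5% level, the detectable differences are about twice those stated: 14 and 15 points for pooled versus control at months 12 and 24, and 16 and 17 points for T1 versus T2 from 70% (14 to 15 from 77–78%). Power at the stated differences is 26% and 30% for pooled versus control and about 28% to 35% for T1 versus T2.

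For pooled versus control the only assumption beyond the document is alpha; for T1 versus T2 it is alpha and the reference rate. Neither changes the conclusion. Because the inputs and the results are printed side by side, this is a stated error and not a detail left to another document. It concerns a primary outcome and should be corrected.

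**What to change.** Keep 330 participants and change the text:

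- State alpha.
- Restate the suppression figures. Pooled versus control: about 14 points at month 12 and 15 at month 24. T1 versus T2: about 16 and 17 points with a 70% reference rate named, or as a range down to 14 to 15 points for a 77–78% reference.
- Replace the d range with about 0.31 to 0.37 on the article's scale (difference divided by 0.458), or name the other scale if 0.35 to 0.42 is reported.
- Remove the description of these suppression effects as small.
- Qualify the upper-bound statement in Sample size and power and the well-powered statement in Limitations so that neither applies to suppression differences of 7 to 9 points. Both may stay for adherence.
- Optionally add a sensitivity range over control rates (pooled, month 12: about 17 points at 50% to 12 points at 80%).

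The cost is wording only. The stated figures become less favourable; sample size, procedures and analysis do not change.
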